### Outcome measures

The primary outcome measure is proportion of clients receiving ≥80 % of their scheduled benzathine penicillin G injections over the 12-month intervention period, compared with the pre-intervention period. This will be calculated using routinely-collected RHD Register data. Data will be anonymised prior to analysis. All outcome measures are shown in Table 4.

**Table 4 Tab4:** Trial outcome measures

Primary outcome	• Proportion of clients receiving 80 % or more of their scheduled benzathine penicillin G (BPG) injections over the 12-month intervention period, compared with the pre-intervention period
Secondary outcomes	• The proportion of scheduled injections that a client receives in a 12-month period • The average number of days at risk. ‘Days at risk’ is the number of days over 28 days between scheduled injections in a month. For clients on 3-weekly injections, ‘Days at risk’ is the number of days over 21 days between scheduled injections • Proportion of clients receiving at least 90 % of scheduled BPG injections over a minimum 12-month period • Proportion of clients receiving 50–79 % and <50 % of scheduled BPG injections over a minimum 12 month period • Recurrence rate and proportion of ARF episodes that are recurrences, compared to non-participating communities and to the whole jurisdiction • Impact of the intervention on RHD clients’ experience of care including their perception and understanding of the disease and its management • Improvement in delivery of other services for RHD clients • Effect of the programme on delivery of other routine services

*ARF* acute rheumatic fever, *RHD* rheumatic heart disease

### Sample size

Using a stepped-wedge design with a 3-month period for each step, with enough communities to provide at least 30 subjects at each step, and taking into account within-cluster correlation, we calculated that 300 clients will provide 90 % power and a two-sided significance level of 5 % to detect an increase from 20 % of subjects receiving ≥80 % of their scheduled penicillin injections to 40 %. This number of clients will provide more than 90 % power to detect a doubling of the rate, if the pre-intervention rate is higher than 20 %. We estimated that health centres at up to 12 communities would be required to ensure a minimum of 300 clients diagnosed with ARF/RHD requiring secondary prophylaxis with penicillin.

The sample size is conservative (i.e. potentially larger than required) as it was calculated based on estimated between-client differences rather than within-client differences, which are usually smaller. That is, since change within a person is what is being measured, and within-client differences (variability within a person) are usually less than between-client differences (variability between people), and lower variance is associated with a lower required sample size, this study will, therefore, be well-powered. We have chosen an ambitious target (doubling the proportion of clients receiving 80 % or more of their scheduled injections) because a complex intervention such as this needs to show a substantial, clinically meaningful benefit if it is to be more widely recommended. The ratio of female to male ARF/RHD clients is approximately 1.3 to 1. Randomisation will be by community, so all ARF/RHD clients requiring secondary prophylaxis in each community will automatically be included.

### Randomisation

Clusters comprise pairs of health centres, entering the study at 3-monthly steps in random order. The random allocation code was generated by the statistician investigator (AK), using StataCorp 2015 Stata Statistical Software: Release 14 (StataCorp LP, College Station, TX, USA). The pairing of health centres was chosen prior to randomisation on grounds of geographical proximity to facilitate travel and minimise project costs, given the very large distances involved. The investigators and the health centres will be informed of the next two centres to commence after the previous centres have been enrolled, to maximise allocation concealment, but also permit adequate time for logistical planning.

This design ensures that all health centres will receive the potential benefits of the intervention while using a robust design (randomisation to intervention timing), and maximising efficiency (study personnel can provide intensive support for different health centres sequentially) [30].

### Data

Data sources chiefly include the NT RHD Register for quantitative analyses, and semi-structured interviews and project officer reports for qualitative analyses. Both provider and client perspectives will be sought, although as the intervention chiefly seeks to change health systems, there will be a particular focus on health provider perspectives. These plus the range of other data sources are listed in Table 5. Important variables included in the RHD Register which will be extracted include client sex, age, date and place of receipt of each penicillin injection during the study period and occurrence of any ARF episodes during the study period.

**Table 5 Tab5:** Sources of data for addressing research objectives

Research objective	Data collection tools	Frequency
1. To test whether a model of care designed to optimise health systems improves adherence to secondary prophylaxis for RHD	• RHD Register data • Spreadsheet of time on intervention for each community	• Continuous
2. To assess the extent to which health clinics change their delivery of RHD care to align with the systems-based model and the barriers and enablers of organisational change	• Systems Assessment Tool (SAT), a component of the One21seventy tool RHD Continuous Quality Improvement package • Project Officer Reports – structured reports from project staff detailing implementation	• Baseline and post intensive phases • Completed at every site visit
	• Semi-structured interviews with clients/carers of clients, clinic managers, RHD coordinators, RHD programme staff, other relevant staff (chronic disease coordinators, NT Health Development public health nurses), using an interview guide for each group of participants	• Mostly baseline and post intensive phases
	• Project Officer Reports	• Completed at every site visit
	• Document review (e.g. meeting minutes, feedback reports from CQI audits)	• As arise
3. To explore the degree to which adopting the systems-based model improves processes of RHD care and adherence to secondary prophylaxis and which elements of the model are most effective in activating change	• RHD SAT and RHD Register	• Baseline and post intensive phases
	• Semi-structured interviews as described above	• Clients/carers: baseline and post intensive phases • Clinic staff and Control Programme staff: baseline and post intensive phases • Other relevant stakeholders: baseline and post intensive phases
	• Project Officer Reports	• Completed at every site visit
4. To explore environmental, organisational and team factors associated with success in achieving organisational and patient-level improvements in secondary prophylaxis for RHD	• RHD SAT and RHD Register	• Baseline and post intensive phases
	• Semi-structured interviews as described above	• Mostly baseline and post intensive phases
	• Project Officer Report	• Completed at every site visit
	• Document review (e.g. meeting minutes, feedback reports from CQI audits)	• As arise
5. To assess the impact of the systems-based model on other services for RHD clients	• RHD CQI audit of ARF/RHD clinical measures, a component of the One21seventy tool RHD Continuous Quality Improvement package	• Baseline and post intensive phases
6. To assess the impact of the systems-based model on other routine services delivered in the clinics	• NT Aboriginal health key performance indicators data	• Baseline and post intensive phases
7. To assess the impact of the intervention on clients’ experience of health care in relation to their ARF/RHD	• Interview guide for RHD clients	• Baseline and post intensive phases

*ARF* acute rheumatic fever, *CQI* continuous quality improvement *NT* Northern territories, *RHD* rheumatic heart disease

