**Methods/Design:**

This trial aims to improve uptake of secondary prophylaxis among Aboriginal people with ARF/RHD to reduce progression or worsening of RHD. This is a stepped-wedge, randomised trial in consenting communities in Australia’s Northern Territory. Pairs of randomly-chosen clinics from among those consenting enter the study at 3-monthly steps. The intervention to which clinics are randomised comprises a multi-faceted systems-based package, in which clinics are supported to develop and implement strategies to improve penicillin delivery, aligned with elements of the Chronic Care Model. Continuous quality improvement processes will be used, including 3-monthly feedback to clinic staff of adherence rates of their ARF/RHD clients.

The primary outcome is the proportion of people with ARF/RHD receiving ≥80 % of scheduled penicillin injections over a minimum 12-month period. The sample size of 300 ARF/RHD clients across five community clusters will power the study to detect a 20 % increase in the proportion of individuals achieving this target, from a worrying low baseline of 20 %, to 40 %. Secondary outcomes pertaining to other measures of adherence will be assessed. Within the randomised trial design, a mixed-methods evaluation will be embedded to evaluate the efficiency, effectiveness, impact and relevance, sustainability, process and fidelity, and performance of the intervention. The evaluation will establish any causal link between outcomes and the intervention. The planned study duration is from 2013 to 2016.

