## Methods/Design

### Study design

This is a stepped-wedge, community randomised trial with an open cohort design. Key characteristics of the trial are shown in Table 2 and Fig. 1. A stepped-wedge trial is a type of cluster randomised trial in which ‘clusters receive the intervention at different time points, the order in which they receive it is randomised, and data are collected from clusters over time’ [29]. The open cohort means that individuals may leave during the trial (no longer require ARF/RHD secondary prophylaxis, die or move to a non-study community), or may become eligible during the trial (receive a new diagnosis of ARF/RHD requiring secondary prophylaxis). Steps of 3 months’ duration were chosen to provide a feasible total study duration whilst providing adequate time for project staff to accomplish intensive visits for incoming clusters. A lag time of 3 months has been anticipated between commencing the intervention and onset of a perceivable effect, hence data collection for quantitative measures during the intervention period will commence 3 months after the onset of the intensive phase for each cluster, providing a 12-month period. Since the intervention is applied at the health centre level, within-cluster correlation has been accounted for in the sample size calculation. Observations will be made on individuals (number of penicillin injections, as documented routinely by the RHD Register, before, during and after the intervention), so the effect of the intervention will be assessed on a within-client basis. Within the randomised trial design, mixed-methods evaluation will take place to address the study objectives.

**Table 2 Tab2:** Characteristics of the ‘Improving Secondary Prophylaxis’ stepped-wedge trial

Term/Trial characteristic	Definition
Unit	Aboriginal health centres
Cluster	Pairs of health centres
Individuals	People with ARF/RHD who require secondary prophylaxis with penicillin, whose primary health centre is enrolled in the study
Timing of start of exposure	Groups of individuals (all individuals managed by a given community clinic) are first exposed at one of a number of discrete time points
Duration of exposure	Fixed length: 15 months per clinic
Measurement	Repeated measurements from individuals: record of every penicillin injection received, as documented in the ARF/RHD Register
Duration of trial	3.5 years
Number of clinics per cluster	2
Total number of clusters	5
Pre-roll out period	11 to 25 months

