### Implementation and project phases

The intervention comprises a set of activities developed and implemented by health centres, aligned under the six themes of the CCM. An additional file shows in detail the types of activities which health centres may adopt (see Additional file 1: Table S1). Implementation is supported by research staff, and progress is monitored using CQI processes. This includes 3-monthly adherence rate reports, presented using simple, coloured graphics and written summaries. Action plans are amended where necessary in response to these reports.

The first (now completed) phase of the project comprised community engagement for recruitment of consenting health centres. The main intervention phases then comprise: (1) *Baseline* data collection and planning (3 months); (2) *Intensive* implementation phase (15 months); (3) *Maintenance* implementation phase (up to 15 months depending on site’s start date) (Fig. 1). In accordance with stepped-wedge trial design, the intervention is implemented at the level of the community/health centre, but measured by its impact on individuals, i.e. clients with ARF/RHD (primary endpoint) and health centre staff (secondary endpoints) [29].

During the 3-month *baseline phase*, project team members visit the health centre for two approximately 5-day visits, one for data collection; the second for planning. Qualitative data including barriers to delivery of secondary prophylaxis at the health centre are identified and recorded through workshops facilitated by the project officer, and an action plan is developed. All site visits, meetings and other arrangements are planned in collaboration with the community stakeholders and health centre staff to mimimise the impact on routine service delivery.

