At commencement of the 15-month *intensive phase*, items in the action plan start being implemented, according to clinic priorities. Potential activities for inclusion in the action plan are listed in Table 3. While necessarily being tailored to local situations, we aim for homogeneity of approaches to ensure similarity of the intervention across sites; this is aided by aligning activities under the six themes of the CCM. All efforts are made to ensure that the exposure to (‘dose’ of) the intervention is uniform across clusters: the duration of intensive phase is identical for each cluster, and the number of scheduled site visits or of episodes of telephone support provided by project staff is uniform. In supporting implementation of the intervention, the research team work closely with health centre staff, CQI facilitators and the NT RHD Control Programme. The action plan is implemented by the health centre staff, supported by the project team. A project team member visits the community monthly, for 1 to 3 days per trip. Visits are supplemented with email and telephone contact.

**Table 3 Tab3:** Potential activities for inclusion in health centre’s action items, grouped under the six streams of the Chronic Care Model

Health system	Delivery system design	Decision support	Clinical information systems	Self-management	Community linkages
Establish a multi-disciplinary RHD working group in health centres comprised of health centre staff and key stakeholders	Allocate, confirm and document responsibility for ARF/RHD care among health centre staff to facilitate planned care interactions and follow-up	Integrate evidence-based guidelines and decision support aids for ARF/RHD into daily clinical practice	Monitor performance of practice team and care system in relation to ARF/RHD care using CQI processes	Up-skill health centre staff in self-management support techniques through engagement with NT Department of Health training activities	Partner with community resources to support timely delivery of SP to ARF/RHD clients

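### As scheduled in Table 5, the measures of other routine services and other RHD services are taken before and after in each clinic, with no concurrent randomised comparison unless each value looks back more than about 3 months

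*Protocol article*

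**What the plan says.** In the Data section, Table 5 pairs each research objective with a data source and a frequency. Objective 6 is "To assess the impact of the systems-based model on other routine services delivered in the clinics" and its source is "NT Aboriginal health key performance indicators data". Objective 5 concerns other services for RHD clients and uses an RHD audit. Objective 7 concerns clients' experience and uses an interview guide. For all three, the only frequency given is the baseline and post-intensive phases. Objective 1, on adherence, uses Register data collected continuously.

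Table 4 lists all three topics as secondary outcomes, one of them as "Effect of the programme on delivery of other routine services". Client experience is worded as an impact, and other RHD services as an improvement. Table 5 words objectives 5, 6 and 7 all as impact. The Abstract adds that the evaluation will establish whether outcomes are caused by the intervention.

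On timing, the Randomisation section says "Clusters comprise pairs of health centres, entering the study at 3-monthly steps in random order", and the section on implementation and project phases says "the duration of intensive phase is identical for each cluster". The statistical methods section assigns outcomes measured at community level to McNemar's test or a paired t test, with covariates added if needed.

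**The concern.** A stepped-wedge trial separates the intervention from calendar time because, at a given date, some clusters have crossed over and others, chosen at random, are still waiting. That protection reaches an outcome only if it is measured in both kinds of cluster over the same period. Two measurements per clinic, tied to the clinic's own phases, may never provide this.

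Objective 6 matters most, because it would show whether effort spent on RHD care displaces other clinic work. The article itself describes other quality-improvement activity in Northern Territory clinics and very high staff turnover. Such influences could move routine indicators with or without this programme, and a before-after difference would credit or blame the programme for them.

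**Working it through.** **Inputs**
- Five clusters (Abstract: "300 ARF/RHD clients across five community clusters"), each a pair of clinics, so 10 clinics.
- Starts 3 months apart, in random order (Randomisation).
- A 3-month baseline phase before each intensive phase (section on implementation and project phases).
- Intensive phase, Table 2: "Fixed length: 15 months per clinic".
- A 3-month lag before intervention-period quantitative data count (Study design).

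**Reproducing Table 2.** Roll-out = 5 × 3 = 15 months, as stated. First and last starts are 4 × 3 = 12 months apart, which matches the post-rollout range (15 − 3 = 12). The pre-roll-out range spans 25 − 11 = 14 months, which does not match 12, so it is tested below.

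**Timeline.** With month 0 as the first intensive start, cluster k starts at s = 3(k − 1). Its baseline runs from s − 3 to s, and its post-intensive measurement comes no earlier than s + 15.

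| Cluster | Baseline (months) | Post-intensive from (month) |
|---|---|---|
| 1 | -3 to 0 | 15 |
| 2 | 0 to 3 | 18 |
| 3 | 3 to 6 | 21 |
| 4 | 6 to 9 | 24 |
| 5 | 9 to 12 | 27 |

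The last baseline ends at month 12 and the first follow-up begins at month 15, a gap of 3 months. If first and last starts were 14 months apart, the gap is 15 − 14 = 1 month; at 15 months apart it is 0. None of these readings gives an overlap. The cause is that the intensive phase (15 months) is at least as long as the spread of start dates.

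**Look-back.** If a value covers the previous L months, the first follow-up window opens at 15 − L. Its overlap with late baselines is max(0, 12 − (15 − L)) = max(0, L − 3):
- L = 0 or 3: 0 months
- L = 6: 3 months
- L = 12: 9 months

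In the last two cases the window covers intensive-phase time, not the post-intensive phase that Table 5 names.

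**Can a time term repair it?** Treat each measurement as a snapshot. A check of the design matrix shows that, with calendar period as a categorical factor, the effect is not estimable, with or without cluster effects. With cluster effects and a linear trend of slope b, every clinic's change equals effect + 18b (15b if baseline is taken at the end of its phase). The interval is the same for all clinics, so effect and trend cannot be separated. Dropping the cluster effects and assuming a linear trend makes the effect estimable, but only by extrapolation.

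**With 3-monthly data for all clinics.** After the lag, cluster k counts as exposed from month 3k; clusters still in their lag are set aside.

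| Months | Exposed clusters | In lag | Waiting |
|---|---|---|---|
| 3 to 6 | 1 | 2 | 3, 4, 5 |
| 6 to 9 | 1, 2 | 3 | 4, 5 |
| 9 to 12 | 1, 2, 3 | 4 | 5 |

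From month 12 no cluster is waiting. Three windows hold both exposed and waiting clinics; the current schedule plans none.

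**The case against.** The strongest reply is that the document never promises a randomised comparison for these outcomes. The Objectives section separates the adherence question from the mixed-methods evaluation, and paired tests are openly before-after. This stands to the extent that the schedule does not contradict the design. The fault lies in the schedule set beside the effect and impact wording.

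A reader might infer that overlap is zero in every case and that no randomised comparison could exist. The document does not support that. Audits and indicators are often period measures, their look-back is not given, and windows of 6 or 12 months would overlap. The Discussion also allows site milestones to move, and a slip of more than 3 months in the last cluster alone could create some unplanned overlap. Even so, a paired test makes no use of calendar time unless a period covariate is added.

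A reader might also infer that Table 4 presents all three outcomes as effects. It does so for two; the third is worded as an improvement, and impact is applied to it only in Table 5. Objective 7 rests on interviews analysed thematically, so only its wording is at issue.

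Counting months 3, 6, 9 and 12 as four usable time points would ignore the plan's lag: at month 3 the only exposed cluster has contributed nothing but lag time.

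Finally, the article does not give the indicators' reporting interval or say whether the audit can be scored for past periods. It also asks that disruption to clinics be kept low and warns of research fatigue. These points limit what can be asked for objective 5.

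**Conclusion.** The point holds for objectives 5 and 6, on the condition that each value is a snapshot or looks back no more than about 3 months. On the stated phases, all baselines then precede all post-intensive measurements by 3 months (1 or 0 on other readings of Table 2), and no calendar period contains both exposed and unexposed clinics. The paired tests give uncontrolled before-after differences, and randomised start order does not protect them from change over the same 15 to 18 months. The consequence is weightiest for objective 6, which Table 4 words as an effect.

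This should be changed, but it concerns supporting outcomes. The primary outcome uses continuous Register data and is not touched.

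**What to change.** - **Objective 6.** In Table 5, replace the two-occasion frequency by extraction of the indicators for all 10 clinics over common calendar periods, 3-monthly or at each reporting period if that is longer, from before the first cross-over to the end of the trial. Analyse them by randomised start order with a calendar-period term and the plan's 3-month lag. State the period each value covers.
- **Objective 5.** Do the same with the audit measures only if existing clinic records allow it without added burden on clinics. Otherwise report the result as a before-after description.
- **Objective 7.** Keep the interviews as planned and describe the result as before-after, not as an effect.

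The cost is a larger data extract and a little more analysis for objective 6, some abstraction time for objective 5 if it is feasible, and wording for objective 7. Precision will be limited: there are five clusters, and in months 9 to 12 only one cluster (two clinics) is still waiting. If the indicators are reported less often than 3-monthly, there will be fewer mixed windows.
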